#### Biomechanical assessment

Following randomisation, participants will undergo a biomechanical assessment to evaluate the immediate effects of the footwear/orthotic intervention on loading (i) beneath the foot, and (ii) on the medial aspect of the first metatarsophalangeal joint and hallux. To assess loading beneath the foot, peak plantar pressures under the toes, forefoot, midfoot and heel will be measured with the in-shoe pedar®-X system (novel GmbH, Munich, Germany), a reliable, valid and accurate measure of in-shoe pressure [37]. The pedar® insoles are approximately 2 mm thick and consist of 99 capacitive pressure sensors, arranged in grid alignment. Plantar pressure data will be sampled at a frequency of 50 Hz. Participants will complete four walking trials for each condition, (i.e., own shoes for control group participants and own shoes *versus* extra-depth shoes with orthoses for intervention group participants). An average recording will be determined from the 16 steps (four steps from four trials) for each condition, which has been shown to be a sufficient number of trials to obtain reliable measurements [37].

To assess loading on the medial aspect of the first metatarsophalangeal joint and interphalangeal joint of the hallux, the pedar®-pad, a highly elastic strap of 256 sensors, will be placed inside the shoe along the medial border of the forefoot (incorporating the first metatarsophalangeal and interphalangeal joints), and peak pressures will be documented. This will be performed in participants’ own most frequently worn closed-in shoes (for control group participants) and own shoes *versus* extra-depth shoes with orthoses (for intervention group participants).

### Primary outcome: feasibility

The primary outcome is feasibility, which will be evaluated according to demand, acceptability, adherence, adverse events and retention rate [38]. The measures and thresholds required to demonstrate feasibility are described below, and a summary is provided in Table 1.

**Table 1 Tab1:** Summary of feasibility outcome measures and thresholds

	*Measure*	*Threshold*
Demand	Recruitment rate	6 participants per month
	Conversion rate	≥ 75%
Acceptability	MOS questionnaire	≥ 75% of the intervention group score more than 5/10 for each of questions 1–6
Adherence		
Footwear/orthoses	Orthotimer® sensor 4-weekly diaries	≥ 75% of participants wear the footwear/orthoses for an average of ≥ 5 h per day
Exercise	PhysiTrack® app / diary	≥ 75% of participants complete at least 24/36 (66%) of the exercise sessions
Adverse events	four-weekly diaries	< 15% and no serious events
Retention rate	Proportion of participants followed up at 12 weeks	≥ 80% retention

#### Demand

Demand will be determined by the recruitment rate (the number of participants recruited per month) and the conversion rate (the proportion of participants providing consent of those who met the selection criteria). The recruitment rate will be considered acceptable if six eligible participants are recruited per month, and the conversion rate will be considered acceptable if ≥ 75%.

#### Acceptability

Acceptability of the intervention will be determined using questions from the Monitor Orthopaedic Shoes (MOS) questionnaire [39] which address issues such as appearance, comfort, weight, and ease of donning and doffing. The intervention will be considered acceptable if ≥ 75% of the intervention group score more than 5/10 for each of questions 1–6.

#### Adherence

Adherence to the footwear/orthoses intervention will be documented using four-weekly diaries and objectively assessed over 12 weeks using a small (9 × 13 × 4.5 mm) temperature sensor embedded in the orthosis (Orthotimer®, Balingen, Germany). Time, date, and temperature measurements will be stored every 15 min, with recordings above 26° Celsius being indicative of shoe wear time [40]. The sensor has previously been validated against objectively measured wear time [40, 41] and is not influenced by ambient temperature fluctuations or physical activity levels [40]. Adherence will be considered acceptable if ≥ 75% of participants wear the footwear/orthoses for an average of ≥ 5 h per day over the 12-week follow-up period. Adherence to the exercise program will be documented using 4-weekly diaries (or the PhysiTrack® smart-phone app) and will be considered acceptable if ≥ 75% of participants attempt at least 66% of the total number of exercise sessions (i.e., 24 out of 36 sessions). In both the control and intervention groups, adherence to the hot/cold packs and bunion pads will be measured using four-weekly diaries.

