#### Intervention group

The intervention group will be provided with the same advice and self-management package as the control group, in addition to:(i)Footwear: high quality, off-the-shelf footwear (Anodyne #45 Sport Jogger; Global Footcare, Coomera, Queensland, Australia). These shoes have been selected as they have an extra-wide toe box and pliable upper material to alleviate pressure on the hallux (Fig. 2). The shoes will be correctly fitted by a research podiatrist, and participants will be asked to wear them as often as possible.(ii)Foot orthoses: prefabricated Formthotics™ (Foot Science International, Christchurch, New Zealand). These orthoses are ¾ length and are constructed from dual-density, closed-cell polyethylene foam (bottom layer 140 kg/m^3^, top layer 60 kg/m^3^). See Fig. 3. Previous research has shown that these orthoses are well accepted, with 81% of participants reporting being ‘somewhat or very satisfied’ with them in a 12 month falls prevention trial [35]. We will use the ¾ length rather than full-length devices as they are less likely to increase dorsal/medial pressure from footwear in people with hallux valgus [36]. The existing insoles will be removed from the shoe to accommodate the orthoses. Participants will be asked to wear these with their footwear as often as possible. At the baseline appointment, minor modifications will be made where necessary to ensure that the orthoses are comfortable.(iii)Foot exercises: participants will be provided with access to a smart-phone app (PhysiTrack®, London, United Kingdom) which demonstrates a home-based version of the progressive resistance foot exercise program developed by Mickle et al. [22]. Participants without access to a smart-phone or personal computer will be provided with a hard copy of the program. The set of nine exercises are performed three times per week for the 12 weeks. Each session takes approximately 30 min to complete. Most of the exercises are performed in a seated position using latex resistance bands wrapped around the toes and/or foot. The exercises target the muscles responsible for ankle dorsiflexion, ankle inversion/eversion, hallux and lesser toe flexion and hallux abduction, and are progressed by either increasing the number of times the exercises are performed (repetitions) or by increasing the level of resistance provided by the bands (light to extra heavy). Adherence to the home-based foot exercise program has been shown to be very high, with 80% of participants (aged 60 to 90 years, 78% women) completing at least 75% of the exercises. The exercises have been shown to increase strength of foot muscles by approximately 20% [22]. Participants will be contacted by the developer of the exercise program ([name]) to address any queries and ensure they are performing the exercises correctly.

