## Discussion

The primary objective of this study is to evaluate the feasibility of conducting a randomised trial comparing multifaceted, non-surgical intervention (footwear, foot orthoses, foot exercises, advice, and self-management) versus advice and self-management alone for reducing pain associated with hallux valgus. Although our recent systematic review [15] identified two studies reporting significant reductions in pain with the use of foot orthoses [19] and exercises [49] in people with hallux valgus, to the best of our knowledge, this is the first study designed to evaluate the effectiveness of these interventions when used in combination, which is more reflective of contemporary clinical practice [14].

A key limitation of the study design is the inability to blind the research staff administering the interventions, however as the outcomes are participant-reported and participants are blinded by limited disclosure, the study can be considered to be assessor-blinded. The most likely barrier to acceptability of (and therefore adherence to) the intervention is aesthetic concerns regarding the footwear. This is a common and largely unavoidable issue with footwear interventions, given their unique role as both a treatment and an item of clothing [50]. Acceptability may be of particular concern in this study, due to the shoes requiring an extra wide toe box to alleviate pressure from the deformity.

The study design has several key strengths, including randomisation, concealed allocation, and blinded analysis, and the reported protocol adheres to the SPIRIT 2013 statement [24] and the CONSORT 2010 statement extension to randomised pilot and feasibility trials [25]. We have selected intervention components that have demonstrated safety and acceptability, are relatively low cost and accessible in the Australian context, so the package of interventions is likely to be easily implemented and scalable if feasibility is demonstrated and the subsequent fully-powered trial demonstrates clinical efficacy. The study design also incorporates objective measurement of adherence, limited efficacy outcome measures addressing the relevant domains of pain and muscle strength, and plantar pressure assessment to provide insights into the potential mechanisms by which footwear and foot orthoses may alleviate loading on the first metatarsophalangeal joint.

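### The only objective measure of footwear/orthoses adherence is a sensor in the orthosis, so it cannot show whether the study shoes were worn, and the merged threshold does not say whether sensor or diary decides

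*Protocol article*

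**What the plan says.** The Intervention group section lists footwear and foot orthoses as separate components, each with its own request to wear it as often as possible. The orthosis is a prefabricated three-quarter-length device that goes into the shoe once the shoe's own insole is taken out. For the orthoses the request reads: "Participants will be asked to wear these with their footwear as often as possible".

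The Adherence section names two instruments for wear of the footwear/orthoses: it is to be recorded in four-weekly diaries and "objectively assessed over 12 weeks using a small (9 × 13 × 4.5 mm) temperature sensor embedded in the orthosis (Orthotimer®, Balingen, Germany"). The sensor's readings are interpreted "with recordings above 26° Celsius being indicative of shoe wear time". Table 1 enters both instruments against the same criterion ("Orthotimer® sensor 4-weekly diaries") and gives a single threshold: "≥ 75% of participants wear the footwear/orthoses for an average of ≥ 5 h per day". Adherence is one of the five domains of the primary feasibility outcome.

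The Discussion states where the sponsor expects difficulty: "The most likely barrier to acceptability of (and therefore adherence to) the intervention is aesthetic concerns regarding the footwear".

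Acceptability is a separate domain. It is assessed with the MOS questionnaire, which Table 3 schedules at baseline and 12 weeks in the intervention group only, and it has its own 75% threshold.

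**The concern.** The criterion is labelled footwear/orthoses, but the objective instrument sits in only one of the two components, and that component is separate from the shoe. A warm sensor shows that the orthosis is in a shoe being worn. Nothing in the article lets it tell the study shoe from another.

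This leaves two possible errors if the sensor decides the criterion:

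- Orthoses moved into a woman's own shoes add to footwear/orthoses adherence although the study shoe is not on her foot.
- Study shoes worn without the orthoses add nothing.

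The first error matters more here. The study shoe was chosen for its extra-wide toe box, and the Discussion expects resistance to exactly that component. The adherence domain could therefore be reported as met when the footwear part of the package was not worn enough, and that result would feed the decision on a full trial.

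**Working it through.** **Inputs from the article**

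- Total sample 28, from 12 per group plus an allowance for 15% drop-out (Sample size).
- 1:1 allocation (Randomisation), so about 14 intervention women. Only they receive shoes and orthoses, so 14 is taken as the denominator.
- Threshold 75% at 5 hours a day or more (Adherence; Table 1).

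**The plan's own sample size.** Adding 15% to 24 gives 24 × 1.15 = 27.6, rounded up to 28. Dividing by the retained fraction gives 24 / 0.85 = 28.2, rounded up to 29. The stated 28 is reproduced to within one participant. It is not in dispute and serves only to fix the group size.

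**Number needed.** 0.75 × 14 = 10.5, so 11 women are needed: 11/14 = 78.6%, while 10/14 = 71.4% falls short.

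**Illustration 1: orthoses moved to other shoes.** Assume all 14 wear the orthoses at least 5 hours a day, and m of them do so only in their own shoes and do not otherwise wear the study shoes.

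| m | Sensor reading | Study-shoe adherence (14 − m)/14 | Study shoe meets 75%? |
|---|---|---|---|
| 0 | 14/14 = 100% | 100% | yes |
| 3 | 14/14 = 100% | 11/14 = 78.6% | yes |
| 4 | 14/14 = 100% | 10/14 = 71.4% | no |
| 7 | 14/14 = 100% | 7/14 = 50% | no |

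The sensor result is the same whatever m is. The two answers part at m = 4.

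**Illustration 2: the reverse.** If all 14 wear the study shoes at least 5 hours a day but 4 always leave the orthoses out, the sensor gives 10/14 = 71.4%, a fail, with study-shoe wear at 100%. The merged figure does not show which component failed.

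**Illustration 3: chance of meeting the threshold.** Assume each woman independently has probability 0.9 of wearing the orthoses at least 5 hours a day, and that a fraction s of those wearers use them only in their own shoes and do not otherwise wear the study shoes. Assume also that women who do not wear the orthoses enough do not wear the study shoes enough either. The chance of passing is P(X ≥ 11) with X binomial, n = 14, and p = 0.9 for the sensor or p = 0.9 × (1 − s) for the study shoe.

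| s | p for study shoe | Pass by sensor | Pass by study-shoe wear |
|---|---|---|---|
| 0 | 0.90 | 0.956 | 0.956 |
| 0.10 | 0.81 | 0.956 | 0.732 |
| 0.25 | 0.675 | 0.956 | 0.283 |
| 0.50 | 0.45 | 0.956 | 0.011 |

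The article gives neither the 0.9 nor any value of m or s. All are assumptions, shown over a range.

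**The case against.** The strongest reply is that the sensor is not the only instrument. The Adherence section and Table 1 both name four-weekly diaries. A reader might infer that adherence is measured by the sensor alone, or that a woman who moves the orthoses to her own shoes is scored as fully adherent. The documents support neither inference. The second holds only so far as the sensor decides, and the article does not say that it does. The diary form is not shown and may already ask about shoes and orthoses separately.

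A reader might also infer that rejection of the shoes would go unseen. That is too strong. The MOS questionnaire asks about appearance and comfort, and its threshold can fail whatever the sensor reads. But it records opinion at two visits, not hours worn: a woman may score the shoe above 5/10 and seldom wear it.

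The request to wear the orthoses with footwear should not be read as permission to use own shoes. In context, after the supplied shoe and the removal of its insole, it most naturally means the study shoe. An instruction still does not show what was worn.

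Finally, one threshold for a package supplied together is a defensible choice, and some operational detail belongs in a fuller document. That is fair for the content of the diary. It does not remove the difficulty that one numerical criterion within the primary outcome has two instruments, which can give different answers, and the objective one cannot see one of the two components. Even a diary that separates the components needs a rule before it can feed a merged threshold.

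**Conclusion.** The point holds in a limited form. The objective measure captures orthosis wear only, the threshold merges orthoses with footwear, and the article does not state which instrument decides. To the extent that the sensor decides, the criterion can be met without adequate wear of the study shoes, the component about which the protocol itself expects resistance.

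With about 14 intervention women, 4 who use the orthoses only in their own shoes are enough to separate a sensor reading of 100% from study-shoe adherence of 71%. This rests on assumed behaviour, so it shows what the criterion could miss and does not predict what will happen. It is a weakness in one criterion of the primary outcome that is cheap to repair, and it does not invalidate the adherence domain.

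**What to change.** In the Adherence section and Table 1, apply and report the threshold of at least 75% of participants at 5 hours a day or more twice: once for orthosis wear, decided by the sensor, and once for study-footwear wear, decided by the four-weekly diary. Call footwear/orthoses adherence acceptable only if both are met. Make sure the existing diary records hours in the study shoes and whether the orthoses were worn in those shoes or in others. The last item is needed because each threshold could be met by wearing the two components apart.

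The cost is revised wording and, if the diary does not already ask, a few more items. Study-shoe wear will rest on self-report, and the reported adherence may be lower. Rejection of the orthoses alone would still fail the combined criterion, but the report would show which component failed.

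Timing is a practical limit. The article was published on 3 June 2022 and expects the 12-week follow-ups to finish by 30 July 2022, so new diary items would reach few participants. If the diaries in use do not record shoe wear, label the sensor result as orthosis adherence, draw no conclusion on footwear wear from it, and carry the separate items into the main trial.

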#### Adverse events

Adverse events will be assessed at four-weekly intervals via postal diary. Participants will be asked to document the type of adverse event, the body location, the frequency and/or severity of the effect. An independent assessor will assess all adverse events as *unrelated*, *probably related* or *definitely related*, and only those considered to be *probably* or *definitely* related will be considered an adverse event. Serious adverse events will be defined as events that are life-threatening, require hospitalisation, or result in persistent or significant disability or incapacity [42]. The rate of adverse events will be considered acceptable if < 15% and none are considered serious.

#### Retention rate

Retention rate is the proportion of recruited participants who complete the 12-week outcome assessment. A ≥ 80% retention rate in each group will be considered acceptable.

### Secondary outcome: limited efficacy testing

The selection of efficacy outcome measures for this trial is based on expert (OMERACT: Outcome Measures in Rheumatology Initiative) guidelines. The key outcome measure is the pain subscale of the Manchester-Oxford Foot Questionnaire (MOXFQ) [43], which has undergone extensive psychometric validation and is recognised as the best condition-specific outcome measure for hallux valgus [44]. The MOXFQ consists of 16 items reflecting three subscales (pain, walking/standing and social interaction). The pain subscale consists of five items scored on a five-point Likert scale (0 to 4; ‘4’ assigned ‘most severe’; higher scores denoting higher severity). The score for each subscale is calculated as the sum of each individual item score and is expressed on a metric of 0 to 100 (100 times actual score, divided by the maximum possible domain score). The MOXFQ pain domain will be measured at baseline and at four-weekly intervals. The pre-specified primary endpoint will be the 12-week score. The minimum clinically important difference for the MOXFQ pain subscale is 12 points [45].

Other limited efficacy outcome measures will include:(i)the MOXFQ [43] walking subscale, measured at baseline and at four-weekly intervals until 12 weeks;(ii)the MOXFQ [43] social subscale, measured at baseline and at four-weekly intervals until 12 weeks;(iii)foot and ankle muscle strength, measured with a hand-held dynamometer using our previously documented, reliable protocol at baseline and week 12 [46];(iv)general health-related quality of life, assessed using Short Form(SF)-12 [47] measured every four weeks;(v)number of participants using co-interventions, documented every four weeks;(vi)participants’ perception of overall treatment effect, assessed with the question “Overall, how has your foot pain changed since the start of the study?” and using a global impression of change 15-point Likert scale response (ranging from ‘a very great deal worse’ to ‘a very great deal better’), measured at 12 weeks [48].

An acceptable feasibility outcome for the limited efficacy testing will be a signal of efficacy for each continuously-scored outcome measure, as evidenced by at least a small effect size (Cohen’s *d* ≥ 0.20, calculated as the difference between the two group means divided by the overall standard deviation), less than 20% use of cointerventions, and a greater than 25% difference in proportion of participants reporting at least ‘somewhat better’ on the perception of overall treatment effect compared to the control group.

A summary of the limited efficacy outcome measures is provided in Table 2, and a summary of standard protocol items is provided in Table 3.

**Table 2 Tab2:** Summary of the limited efficacy outcome measures

*Measure*	*Threshold*
MOXFQ subscales	small effect size (*d* ≥ 0.20)
Muscle strength	small effect size (≥ 0.20)
SF-12	small effect size (*d* ≥ 0.20)
Use of cointerventions	< 20%
Perception of overall treatment effect	≥ 25% difference in proportion of participants reporting at least “somewhat better” compared to control group

**Table 3 Tab3:** Summary of standard protocol items

	T0	T1 Baseline (lab)	T2 4 weeks (postal)	T3 8 weeks (postal)	T4 12 weeks (lab)
Postal invitation	X				
Telephone screening	X				
Informed consent		X			
Baseline assessments					
Medical history questionnaires		X			
3D foot scanning		X			X
Biomechanical assessment		X			
Randomisation		X			
Receive intervention		X			
CEQ		X			
MOS (intervention group only)		X			X
Outcome measures					
MOXFQ		X	X	X	X
Muscle strength		X			X
SF-12		X	X	X	X
Use of cointerventions		X	X	X	X
Incidental and planned activity questionnaire		X	X	X	X
Perception of overall treatment effect			X	X	X
Adherence					
Footwear/orthoses		continuous (Orthotimer®)			
Exercise		continuous (PhysiTrack® app)			
Adverse events		X	X	X	X

### Data management

Hard copy baseline and follow-up questionnaires will be stored in a locked filing cabinet at La Trobe University and then shredded after being transferred into electronic formats for analysis (Microsoft Excel; Microsoft Corporation, Redmond, Washington, USA, and IBM SPSS Statistics; IBM Corporation, Armonk, New York, USA). Other data files (3D foot scans and plantar pressure files) will be stored in native file formats on a password-protected university server and will be securely deleted following de-identification and transfer to electronic formats for analysis.

### Statistical analysis

As this is a feasibility study, it is not powered to detect changes in outcome measures, so the focus will not be on inferential testing. Descriptive statistics will be used to report feasibility outcomes. Mean (SD) scores and mean differences (95% CI) will be used to explore differences in continuous variables between the groups. Differences in the MOXFQ pain subscale between groups at 12 weeks (analysis of covariance, adjusted for baseline differences) will be used to inform the sample size calculation for the main randomised trial.

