Of the available non-surgical treatments, the most widely used are footwear, foot orthoses and foot exercises [14], and there is preliminary evidence supporting the use of these approaches. Ill-fitting footwear is an important modifiable risk factor for the development and progression of hallux valgus, as it has been shown that the likelihood of having the condition is significantly greater in those who have worn shoes with a very narrow toe box between the ages of 20 and 29 years [16]. Furthermore, if the condition is already present, the provision of extra-depth footwear which accommodates the broader forefoot may reduce pain [17]. Foot orthoses have been shown to reduce load under the great toe and medial midfoot in people with hallux valgus [18], and a randomised trial reported a significant reduction in pain at six months those who received this intervention [19]. As hallux valgus progresses, the malalignment of the first metatarsophalangeal joint results in decreased muscle size [20] and subsequent weakness of the muscles responsible for hallux plantarflexion and abduction [21]. However, a recent trial of older people (78% women) found that a progressive, resistance exercise program improved hallux plantarflexion strength by approximately 20% over 12 weeks and resulted in an improvement in perceived foot health [22].

The available evidence provides preliminary support for the use of footwear, foot orthoses and foot exercises for the treatment of hallux valgus, but these three promising approaches are yet to be evaluated in combination. Therefore, the primary objective of this study is to evaluate the feasibility of conducting a randomised trial comparing multifaceted, non-surgical intervention (footwear, foot orthoses, foot exercises, advice, and self-management) versus advice and self-management alone for reducing pain associated with hallux valgus. The secondary objective is to obtain statistical parameters to inform the main trial sample size calculation and provide a signal of efficacy to justify the future main trial.

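### The effect size that decides the efficacy signal has no baseline term, although baselines are collected and ANCOVA is named for MOXFQ pain; adjusting all of them is a modest, nearly free gain

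*Protocol article*

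**What the plan says.** Under Statistical analysis, the general rule for continuous outcomes is: "Mean (SD) scores and mean differences (95% CI) will be used to explore differences in continuous variables between the groups". No covariate is named. The next sentence names baseline adjustment once, for one outcome and for one purpose, which is to plan the size of the main trial. It opens: "Differences in the MOXFQ pain subscale between groups at 12 weeks (analysis of covariance, adjusted for baseline differences) will be used to inform the".

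The signal is defined under Secondary outcome: limited efficacy testing. The plan looks for "a signal of efficacy for each continuously-scored outcome measure, as evidenced by at least a small effect size", with d of at least 0.20, and gives the formula: "calculated as the difference between the two group means divided by the overall standard deviation". Table 2 applies the 0.20 threshold to the MOXFQ subscales, muscle strength and SF-12. Table 3 shows a baseline and a 12-week measurement for each of these.

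For MOXFQ pain, "The MOXFQ pain domain will be measured at baseline and at four-weekly intervals", and "The pre-specified primary endpoint will be the 12-week score". No time point is attached to d for the other outcomes.

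The signal has a stated use: part of the secondary objective in the Background is to "provide a signal of efficacy to justify the future main trial".

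**The concern.** The formula for d is written out, so the question is whether a stated rule is well chosen, not whether a detail is missing. As it stands, the rule makes no use of the baseline score. In a trial of 28 women the arms will often differ at baseline by chance, and part of that difference persists to follow-up in proportion to the baseline-to-follow-up correlation. Against a threshold as low as 0.20 SD, the part carried over can settle whether an outcome shows a signal.

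MOXFQ pain, the key efficacy measure, would also carry two estimates in one report: a d without a baseline term for the signal, and an ANCOVA difference for planning. The protocol does not say which is to be believed if they point different ways.

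**Working it through.** **Inputs from the protocol.** Target of 12 per group, 15% drop-out and 28 recruited (Sample size); 1:1 permuted blocks with no stratification mentioned (Randomisation); threshold d ≥ 0.20 (limited efficacy testing and Table 2).

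**Assumption.** The correlation r between baseline and follow-up is not in the documents. The range 0.3 to 0.7 is used throughout.

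**The plan's own figure.** 24 × 1.15 = 27.6, so 28; the alternative 24 / 0.85 = 28.2 is within one participant of it. The recruited number reproduces, and the evaluable number lies between 12 and 14 per arm.

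**Chance baseline gap.** The SD of the standardised baseline difference is √(2/n): √(2/12) = 0.408 and √(2/14) = 0.378. By the normal approximation, counting both directions:
- gap ≥ 0.2 SD: 62% (12 per arm), 60% (14 per arm)
- gap ≥ 0.4 SD: 33% (12 per arm), 29% (14 per arm)

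**What carries over.** A gap g adds r × g to the follow-up difference. At r = 0.5, a gap of 0.4 SD adds 0.5 × 0.4 = 0.20 SD, the whole threshold.

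**Precision.** The ratio of the ANCOVA to the unadjusted standard error is √(1 − r²) × √(1 + 1/(2n − 4)), where the second factor is the price of estimating the slope. At n = 12 that factor is √1.05 = 1.025.
- r = 0.3: 0.954 × 1.025 = 0.98, a 2% reduction
- r = 0.5: 0.866 × 1.025 = 0.89, an 11% reduction
- r = 0.7: 0.714 × 1.025 = 0.73, a 27% reduction

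**Pass rates.** Simulation of 100,000 trials per setting, normal data, d = difference / overall SD, adjusted with the pooled within-group slope. Share of trials with d ≥ 0.20 at 12 per arm:

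| True effect | Unadjusted | Adjusted, r = 0.3 | r = 0.5 | r = 0.7 |
|---|---|---|---|---|
| 0 | 0.32 | 0.31 | 0.30 | 0.26 |
| 0.5 SD | 0.77 | 0.78 | 0.80 | 0.85 |

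At 14 per arm with no true effect, 0.30 becomes 0.30, 0.28 and 0.24.

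**Disagreement.** Over 12 and 14 per arm, r from 0.3 to 0.7 and true effects of 0 or 0.5 SD, the two versions of d fall on opposite sides of 0.20 in about 7-22% of trials. With no true effect and 14 per arm the figures are 9%, 14% and 21% for r = 0.3, 0.5 and 0.7.

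**When a large gap does occur.** With no true effect, 14 per arm and a gap of at least 0.4 SD:

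| Gap | Unadjusted passes (r = 0.3, 0.5, 0.7) | Adjusted passes |
|---|---|---|
| favours intervention | 48%, 61%, 77% | about 24-31% |
| favours control | 16%, 7%, 2% | about 24-31% |

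**The case against.** The strongest reply is that adjustment hardly changes the error rate. Randomisation keeps the unadjusted difference unbiased over repeated trials. The disagreement rate is not an error rate, because the adjusted value is not the truth either and many disagreements cancel. With no true effect an outcome still passes in roughly a quarter to a third of trials after adjustment, since 0.20 is only about half of the 0.38-0.41 standard error. The larger weakness is a point-estimate threshold at this sample size. All of this stands and limits the size of the point. It does not remove it: in the particular trial that is run, a large gap makes the unadjusted verdict depend on which arm it favours, and the data to correct this are already in hand.

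Several stronger readings are tempting but not supported:

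- **Every outcome uses raw 12-week means.** This is the natural reading, but an inference. The article does not say raw, ties only MOXFQ pain to 12 weeks, and neither states nor excludes change scores. Covariates for the general summaries may be set in an analysis plan that is not shown. The criticism therefore rests on the explicit formula for d.
- **Imbalance drives the signals, or d is a formal go/no-go rule.** Imbalance accounts for r² of the variance of d: 9%, 25% and 49% at r = 0.3, 0.5 and 0.7. The primary outcome is feasibility, and Table 1 contains no effect size. The signal serves to justify a main trial, but no binding decision rule is written.
- **Two estimates for MOXFQ pain contradict each other.** They serve different purposes, and reporting both is not an error. One estimate is simply cleaner.
- **The overall SD is a faulty denominator.** It is openly stated, and at the threshold it is immaterial: 0.200 / √(1 + 0.2²/4) = 0.199. Nor is a pooled baseline SD required; entry demands pain of at least 3 out of 10, which could narrow the baseline spread and inflate d.

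**Conclusion.** The point holds in a limited form. The stated d for the efficacy signal omits the baseline, while the same article collects baseline MOXFQ, strength and SF-12 and already names "analysis of covariance, adjusted for baseline differences" for one of them.

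The benefit of adjusting is real but modest, and depends on the assumed r of 0.3 to 0.7. At r = 0.3 it is close to nothing (2% in standard error); at r = 0.7 it is worthwhile (27%). What adjustment buys is a verdict that no longer depends on the direction of a chance baseline gap. It does not make 0.20 a reliable threshold at 12 to 14 per arm, and should not be presented as doing so.

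**What to change.** Under limited efficacy testing, Statistical analysis and Table 2, define d for each continuous outcome with a baseline value as the ANCOVA-adjusted 12-week mean difference divided by a stated SD, reported with the 95% CI of the difference. The overall SD may stay. Sign d so that positive favours the intervention, since higher MOXFQ scores mean greater severity whereas higher strength is better. For MOXFQ pain, use this one estimate for both the signal and the sample size.

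The cost is a change of wording and one degree of freedom per model. No new data are needed.
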